## 6.2 Randomisation, blinding and treatment allocation

Participants will be allocated to either the treatment group or control group at random by means of randomisation on the factors: site, gender and participation in fMRI substudy. We will correct for randomisation factors in the analysis, in order to prevent bias. At all sites experienced interviewers are available that will be blinded to the study condition. Interviewers remain blind to the treatment allocation, but patients cannot be blinded after care allotment.

## 6.3 Study procedures

Chapter 2 shows a flow chart of the study design and main procedures. Onsite therapists will screen patients based on seven selection questions. Selected patients will be contacted and asked if they are interested in participating in the study. Interested patients will be sent an information letter. Two weeks after receipt of the information letter, patients will be contacted again to ask whether they decided to participate in the study and whether they would like to participate in the additional MRI sub-study. Subsequently, a selection assessment is planned in order to check whether patients meet the inclusion criteria by means of two interviews and if applicable, to fill out an MRI-checklist. When patients are eligible for participation, an informed consent form will be obtained.

If a patient does not meet the criteria, he/she will be excluded from the study. The assessor will call the patient and tell that he/she cannot participate but will receive 10 euros compensation for the selection assessment. With patients who meet the selection criteria a baseline assessment is planned. During this appointment of approximately 160 minutes, patients will fill out several questionnaires. During this appointment, participants receive an accelerometer.

They will be instructed to hand in the device at the following appointment. Patients who are also interested in participating in the MRI sub-study and meet the additional MRI criteria, are asked for a pretest MRI session. During this appointment of approximately 90 minutes participants will perform two tasks in an MRI scanner. After the pretest(s), participants will either receive the psychomotor assertiveness training consisting of 20 weekly training sessions (treatment-group) or befriending sessions (control-group). The last session, participants again receive an accelerometer. They will be instructed to hand in the device at the post assessment. Within two weeks after the last intervention session, a posttest assessment will take place. The appointment will take approximately 180 minutes. With patients who also participate in the MRI sub-study, a posttest MRI session will be planned. After six months, participants will be contacted again for a follow-up assessment consisting of questionnaires similar to the earlier pre- and posttest assessment. Respectively, a year and two years later, participants will be contacted for a second and third follow-up assessment. These assessments will take approximately 110 minutes and consists of an interview and questionnaires. More details about the selection and pre- and posttest instruments can be found in paragraph 5.1. Table 5 shows the study design of the instruments (see appendix F for instruments). The selection assessment, pre- and posttest assessments, follow-up assessments with questionnaires and the intervention sessions will take place at the mental health care institutions. The MRI sub-study will take place at the Neuroimaging Centre in Groningen.

Table 5: study design of the instruments

| Instruments                                      | Pre-selection | Selection | Pre-assessment | Post-assessment | Follow-up I | Follow-up II | Follow-up III |
|---------------------------------------------------------|----------------------|------------------|-----------------------|------------------------|--------------------|---------------------|----------------------|
| Selection criteria evaluated by onsite therapist        | x                    |                  |                       |                        |                    |                     |                      |
| Positive and negative symptoms *(PANSS)                 |                      | x                |                       | x                      | x                  | x                   | x                    |
| Brief negative symptom scale * (BNSS)                   |                      | x                |                       | x                      | x                  | x                   | x                    |
| MiniSCAN                                                |                      | x                |                       |                        |                    |                     |                      |
| Integrale veiligheidsmonitor (IVM)                      |                      |                  | x                     | x                      | x                  | x                   | x                    |
| Revised Conflict Tactics Scale (CTS2)                   |                      |                  | x                     | x                      | x                  | x                   | x                    |
| Self-expression and control (ZECV)                      |                      |                  | x                     | x                      | x                  |                     |                      |
| Internalized stigma of mental illness (ISMI)            |                      |                  | x                     | x                      | x                  |                     |                      |
| Self-esteem rating scale – short form (SERS-SF)         |                      |                  | x                     | x                      | x                  |                     |                      |
| Screening Risico Verslavingsproblemen (Substance abuse) |                      |                  | x                     | x                      | x                  | x                   | x                    |

|                                                     |  |   |   |   |   |   |   |
|-----------------------------------------------------|--|---|---|---|---|---|---|
| Schaal Interpersoonlijk Gedrag (SIG)                |  |   | x | x | x |   |   |
| Faux pas task                                       |  |   | x | x | x |   |   |
| Wall of faces task**                                |  |   | x | x |   |   |   |
| Emotional faces paradigm**                          |  |   | x | x |   |   |   |
| Trauma Screening Questionnaire (TSQ)                |  |   | x | x | x | x | x |
| Social functioning scale (SFS)                      |  |   | x | x | x | x | x |
| Nationale herstelschaal (NHS)                       |  |   | x | x | x | x | x |
| Manchester short quality of life (MANSA)            |  |   | x | x | x | x | x |
| Biographical questionnaire                          |  |   | x |   |   |   |   |
| Accelerometer                                       |  |   | x | x |   |   |   |
| Other type of accelerometer                         |  | x |   |   |   |   |   |
| Modified Shuttle Test (MST)                         |  |   | x | x |   |   |   |
| Simple physical activity questionnaire (SIMPAQ)     |  | x | x |   |   |   |   |
| Montreal Cognitive Assessment (MoCA)                |  | x |   |   |   |   |   |
| DSM 5 vragenlijst algemene psychiatrische symptomen |  | x |   |   |   |   |   |

\* PANSS and BNSS scores obtained during selection are also used as baseline measure.

\*\* In case of participation in the MRI-substudy

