#### 6.1.2 Main study parameters/end point

The main study parameters and subsequent instruments used in this study are shown in table 4.

Table 4: Main study parameters

| Parameter                         | Instrument                 | Duration   | Type                     |
|-----------------------------------|----------------------------|------------|--------------------------|
| Primary outcome measures   |                            |            |                          |
| Victimization                     | IVM                        | 10 minutes | Self-rating              |
|                                   | CTS2                       | 20 minutes | Self-rating              |
| Mediating factors          |                            |            |                          |
| Social cognition                  | Faux pas task              | 20 minutes | Neuropsychological task  |
|                                   | Wall of faces task**       | 20 minutes | fMRI task                |
|                                   | Emotional faces paradigm** | 15 minutes | fMRI task                |
| Self-expression and control       | ZECV                       | 10 minutes | Self-rating              |
| Internalised stigma               | ISMI                       | 15 minutes | Self-rating              |
| Social behavior                   | SIG                        | 15 minutes | Self-report              |
| Self-esteem                       | SERS-SF                    | 10 minutes | Self-rating              |
| Secondary outcome measures |                            |            |                          |
| Quality of life                   | MANSA                      | 5 minutes  | Self-rating              |
| Trauma                            | TSQ                        | 5 minutes  | Self-rating              |
| Recovery                          | NHS                        | 10 minutes | Self-rating              |
| Societal participation            | SFS                        | 20 minutes | Self-report              |
| Negative symptoms                 | BNSS in addition to PANSS  | 30 minutes | Semistructured interview |
| Fitness                           | MST                        | 15 minutes | Physical test            |
| Physical activity                 | Accelerometer              | 1 week     | Physical measure         |

\*IVM= Integrale Veiligheidsmonitor

CTS2= Revised Conflict Tactics Scale

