### **Accelerometer**

Accelerography is a valuable tool for motion analysis in psychiatry (Teicher 1995). It has been used in psychosis to study sleep and circadian rhythms (Haug et al., 2000; Hofstetter et al., 2005; Martin et al., 2005; Poyurovsky et al., 2000; Shamir et al., 2000; Wulff et al., 2006). However, data on quantitative motor activity can also be obtained using accelerometers (Farrow et al., 2005; Farrow et al., 2006; Walther et al., 2009). All subjects will wear an accurate and validated accelerometer for the continuous recording of motor activity. The accelerometer is a light and small device which can be worn at the wrist, ankle or hip.

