#### 6.5 Replacement of individual participants after withdrawal

Participants who withdraw from the study, will not be replaced.. Participants who withdraw from the study will still be invited for post-treatment assessment and follow-up.

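### Post-treatment accelerometer hand-out depends on attending the last session and has no minimum wear interval, so activity data can be selectively missing or shorter than one week

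*Protocol*

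**What the plan says.** Protocol section 6.3 describes two accelerometer measurements. The first device is given out at the baseline assessment and returned at the next appointment. For the second, the text reads: "The last session, participants again receive an accelerometer. They will be instructed to hand in the device at the post assessment". The timing of that return visit is given as: "Within two weeks after the last intervention session, a posttest assessment will take place". This sets a latest day and no earliest day.

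Three other places bear on the point:

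- Table 4 in section 6.1.2 lists physical activity among the secondary outcome measures, with the row "Physical activity | Accelerometer | 1 week | Physical measure".
- The accelerometer paragraph in section 6.1.2 states: "All subjects will wear an accurate and validated accelerometer for the continuous recording of motor activity". Table 5 marks the device at the pre- and post-assessments.
- Section 6.5 states: "Participants who withdraw from the study will still be invited for post-treatment assessment and follow-up".

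The Protocol describes no other hand-out route for someone absent from the last session, and no minimum time between hand-out and return at either measurement.

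**The concern.** Most post-assessment measures are collected at the visit itself, so anyone who comes can supply them. The accelerometer is different, because its data must be recorded before the visit. By placing the hand-out at the last training or befriending session, section 6.3 makes the existence of the outcome depend on being present at that session.

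Presence at the end of a 20-session programme is a post-randomisation event. The two programmes are very different, one built on kickboxing exercise and the other on befriending, so attendance may differ between arms. Staying in an exercise programme is also plausibly related to how active a person is. A comparison limited to those still attending would no longer be a comparison of the groups as randomised, and analysis cannot fully recover recordings that were never made.

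The second issue is duration. With no earliest day for the post assessment, a visit soon after the last session shortens the recording below the stated week, and a part-week can miss weekdays or weekend days.

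**Working it through.** No sample-size or power figure underlies this point. The check sets the stated steps side by side and does simple interval arithmetic.

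**Step 1: who can receive the post-treatment device.**

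| Situation | Baseline | Post-treatment |
|---|---|---|
| Hand-out point (6.3) | Baseline assessment | Last session |
| Depends on attending sessions? | No, sessions have not started | Yes |
| Return point (6.3) | Following appointment | Post assessment |
| Minimum interval stated? | No | No |

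For a participant absent from the last session, the first remaining contact that the Protocol describes is the post assessment, which is also the return point. Time available for recording before return is therefore 0 days. Section 6.5 nevertheless wants withdrawn participants assessed, and section 6.1.2 wants all subjects to wear the device. The hand-out step does not deliver what those two statements intend.

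**Step 2: how long an attender can record.** Let day 0 be the last session, when the device is given, and let d be the day of the post assessment. Section 6.3 allows d from 0 to 14. Table 4 needs 7 days.

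- Obtainable part of the required week = min(d, 7).
- d = 0 gives 0 days; d = 1 gives 1; d = 3 gives 3; d = 6 gives 6; d = 7 gives 7; d = 14 gives 7.

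Visits on days 0 to 6 fall short of the stated week; visits on days 7 to 14 do not. The schedule permits a short recording but does not require one.

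**Step 3: size.** The share of short recordings equals the share of visits booked before day 7. The Protocol gives no distribution of visit days. If every visit is on day 7 or later the share is 0%; if every visit is earlier it is 100%. The share with no device equals the share absent from the last session, and the Protocol gives no session-attendance rate. Neither quantity can be narrowed from the text.

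**Step 4: is there room for a remedy?** A 7-day recording inside a 14-day limit leaves 14 − 7 = 7 days of slack. A device received by day 7 can still give a full week before the two-week limit. The bookable days for someone given the device on day 0 fall from 15 (days 0 to 14) to 8 (days 7 to 14).

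**The case against.** The strongest reply is that the argument rests on silence. Nothing in the Protocol says that absentees are refused a device. The statement that all subjects wear it, the mark at post-assessment in Table 5 and the invitation in section 6.5 together show an intention to measure them. Section 6.3 could be read as the routine for attenders, with delivery to others left to site logistics. This stands in part: it would be wrong to say that non-attenders will get no device. It does not remove the point, because section 6.3 does state an operational step, and that step taken alone leaves those people without a recording week. Nor does it help to read the last session as each person's own last one, since someone who stops without notice cannot be handed a device on that day.

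A second reply is that one week of wear fits inside two weeks, so the passages on duration do not contradict each other. That is correct. A reader might infer that recordings will be shorter than a week; the text supports only that they can be.

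A reader might also take the 25% drop-out in the sample-size section as the share who would go without a device. The Protocol does not support that. The 25% is an allowance for drop-out in the sample-size calculation, not a session-attendance rate. People lost altogether would have no post-treatment recording wherever the device was handed out, and those who stop sessions may also miss the post visit. Likewise, any single percentage for short recordings would rest on an assumed spread of visit days.

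Finally, the outcome is peripheral. Physical activity is one of seven secondary measures in Table 4, and the secondary outcomes named in the Summary do not include it. This stands and limits the weight of the point.

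**Conclusion.** The point holds in a limited form. As written, section 6.3 gives participants who stopped, or who missed the last session, no stated way to receive a device before the post assessment. Whether post-treatment activity data exist can therefore depend on attendance after randomisation. Section 6.3 also allows a return visit too early for the one week in Table 4, while visits on days 7 to 14 comply.

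The size is unknown. Short recordings could be anywhere from 0% to 100% depending on booking, and the number without a device depends on attendance figures that the Protocol does not give. Selective loss further assumes that sites follow section 6.3 literally and that attendance is related to activity or differs by arm; both are plausible, neither is documented. The missing minimum interval applies to the baseline device too, but the dependence on session attendance is confined to the post-treatment one. The primary victimization outcome, the mediators and the sample size are untouched. The change is worth making because it is cheap and recordings not made cannot be recovered later.

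**What to change.** In section 6.3, separate the post-treatment device from the last session:

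- Give or send it to every randomised participant who is due a post assessment, whether or not they attend the last session.
- Schedule return at least 7 full days after the participant receives the device, within the existing two-week limit where possible. For a device that is sent, count from receipt, not from the session; receipt by day 7 keeps return inside the limit.
- Apply the same minimum of 7 full days to the baseline device, which is now due back at the following appointment with no interval stated.

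Section 6.3 would then agree with Table 4, the accelerometer paragraph and section 6.5. The cost is Protocol wording, a minor delivery expense for non-attenders and a narrower booking window. Where a device reaches a participant late, the site may have to choose between the full week and the two-week limit, and the text should say which takes priority.

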#### 6.4 Withdrawal of individual participants

Participants can leave the study at any time for any reason if they wish to do so, without any consequences. The investigator can decide to withdraw participant from the study for urgent medical reasons.

#### 6.5 Replacement of individual participants after withdrawal

Participants who withdraw from the study, will not be replaced.. Participants who withdraw from the study will still be invited for post-treatment assessment and follow-up.

## **7. SAFETY REPORTING**

### **7.1 Section 10 WMO event**

In accordance to section 10, subsection 1, of the WMO, the investigator will inform the participants and the reviewing accredited METC if anything occurs, on the basis of which it appears that the disadvantages of participation may be significantly greater than was foreseen in the research proposal. The study will be suspended pending further review by the accredited METC, except insofar as suspension would jeopardise the participants' health. The investigator will take care that all participants are kept informed.

### **7.2 Adverse events (AEs)**

None of the previous studies on exercise therapy or PMT, nor the feasibility study indicate any risk of adverse events. Furthermore, we do not foresee any problems caused by kickboxing. Although kickboxing is sometimes associated with aggression in the media there is no scientific prove that kickboxing itself induces aggressive behaviour. As shown in chapter 1 there are other explanations for the associated aggression. This is consistent with the findings of the pilot. In no way this training has been harmful for patients or for the people in their environment. Participants find the training enjoyable and experience a decrease rather than an increase in anger and aggression.

To prevent physical injuries, all exercises are carefully build-up during the training and participants can participate on their own physical level. It is possible that some participants will experience minor muscle aches after the training, especially those who are not used to physical exercise. Although participants learn how to be careful, adapt their kickboxing moves and use boxing gloves, shin guards and punching bags it is possible that someone will get a small bruise. Both the muscle ache and the bruise will disappeared in a few days and are not considered as health risks.

As shown in the exclusion criteria, in case of pregnancy, a participant cannot participate.

In case anything unforeseen happen, CCMO will be informed immediately. All adverse events reported spontaneously by the participant or observed by the investigator or his staff will be recorded.

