**Nature and extent of the burden and risks associated with participation, benefit and group relatedness**

For all participants, the selection assessment will take approximately 60 minutes, the pre-test will take approximately 160 minutes, the pos-test will take approximately 180 minutes, the first follow-up assessment takes 180 minutes and the second and third follow-up assessment will take approximately 110 minutes. For the participants in the fMRI study, the pre- and post MRI appointments will both take approximately 90 minutes. For participants randomised in the experimental group, the intervention consists of 20 sessions of 75 minutes. For participants randomised in the control group, 20 befriending sessions are organised. In the media material arts are sometimes associated with aggressive behavior. However, most research does not support this finding or shows opposite results. It is unlikely that kickboxing in itself increases aggressive behavior. Based on a recent feasibility study we don't expect any adverse events to happen for this reason and consider no such risks to be associated with participation.

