### **Revised Conflict Tactics Scale**

The revised Conflict Tactics Scale (CTS2) measures to what extent the respondent is involved in a psychological or physical attack and the use of reasoning or negotiation to deal with conflicts (Straus, Hamby, Boney-McCoy, & Sugarman, 1996). The CTS2 is a widely used instrument in partner violence research and consist of 39 behavior items. Participants report how many times, ranging from 1 'has never happened' to 8 'more than twenty times' the items apply on themselves or their partner in a given time period (Vega & O'Leary, 2007). Since we are interested in a broader range of social interactions we changed the questions from 'partner' to 'someone'. For example 'I kicked my partner' and 'My partner did this to me' is changed in 'I kicked someone' and 'Someone did this to me'. The CTS2 assesses more subtle forms of victimization, therefore this instrument is a good addition to the IVM.

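### Aggressive acts outside the sessions would largely go unrecorded as harm, although the CTS2 already asks about them in both arms and no between-arm comparison is planned

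*Protocol*

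**What the plan says.** **Harm collection.** Section 7.2 gives one rule: "All adverse events reported spontaneously by the participant or observed by the investigator or his staff will be recorded". Section 7.1 (suspension and notification) and Section 9.3 (annual report) add reporting duties but no further way of collecting events. Muscle ache and small bruises are expected, and Section 7.2 says they "are not considered as health risks".

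**Aggression as a safety question.** The Summary states: "It is unlikely that kickboxing in itself increases aggressive behavior". Section 1 argues the same at length, and Section 7.2 repeats: "Although kickboxing is sometimes associated with aggression in the media there is no scientific prove that kickboxing itself induces aggressive behaviour".

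**The CTS2.** Section 6.1.2 says that it "measures to what extent the respondent is involved in a psychological or physical attack and the use of reasoning or negotiation". Items come in pairs, one with the respondent as actor and one as target; the partner wording of the example pair "is changed in 'I kicked someone' and 'Someone did this to me". Answers are frequencies, from never to more than twenty times. The stated reason for including it is victimization alone: "The CTS2 assesses more subtle forms of victimization, therefore this instrument is a good addition to the IVM". Table 4 lists it, with no subscale named, beside the IVM as a primary outcome measure. Table 5 schedules it at pre-assessment, post-assessment and follow-ups I, II and III.

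**Analysis.** Section 8.2 covers long-term victimization, general long-term outcomes and the risk factors. It names no comparison of harms or of own aggression.

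**The concern.** A rule based on volunteered reports and staff observation suits injuries in the gym. It does not suit acts committed elsewhere against other people, which staff do not see and participants have little reason to volunteer. Yet Section 7.2 makes a reassuring statement about the people around the participant as well as the participant. At the end of the trial, few recorded aggressive incidents would be hard to interpret: there may have been few, or few may have been reported.

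The trial already collects better information and gives it no safety role. The same instrument raises a second issue. The Summary says that both primary questionnaires examine whether someone was a victim, while the CTS2 as described also covers own attacks and negotiation. The protocol does not say which items make up the victimization score. If items of all three kinds entered it, the primary outcome would include aggression, which the protocol treats as a mediator, and conflict handling, which Module 2 trains through de-escalation.

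**Working it through.** The protocol gives no figure on this point to reproduce. The check is mainly a comparison of passages, with two short calculations for scale.

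**Step 1. What is collected on aggression, and in what role**

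| Source | Content | When, in both arms | Role in the plan |
|---|---|---|---|
| Section 7.2 | Events volunteered or seen by staff | Unscheduled | Adverse events |
| ZECV (6.1.2, Tables 4 and 5) | Anger expression and control | Pre, post, follow-up I | Mediating factor |
| MANSA (6.1.2, Tables 4 and 5) | One item on accusation of crime in the past year | Pre, post, follow-ups I–III | Quality of life |
| CTS2 (6.1.2, Tables 4 and 5) | Frequency of attacks made and suffered; negotiation | Pre, post, follow-ups I–III | Primary victimization measure |

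Of the instruments described, only the CTS2 asks how often participants attacked someone, and it runs to the last follow-up. None is assigned to harm.

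**Step 2. How much data this is.** Up to 120 participants × 5 assessments = 600 questionnaires. With the 25% drop-out in the sample size calculation, 120 × 0.75 = 90 participants (45 per arm) would remain.

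**Step 3. What incomplete capture costs (illustration).** The protocol gives no rate of own aggression. Assume that 20% of one arm and 40% of the other attack someone at least once, with n = 60 per arm and two-sided α = 0.05, and that passive recording catches a fraction s of cases equally in both arms.

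Power = Φ[(|p1 − p2| − 1.96·√(2p̄(1 − p̄)/n)) / √((p1(1 − p1) + p2(1 − p2))/n)]

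- s = 1: p̄ = 0.30; 1.96 × √(0.42/60) = 0.164; √(0.40/60) = 0.0816; (0.200 − 0.164)/0.0816 = 0.44; power 67%.
- s = 0.75 (15% v 30%): power 50%.
- s = 0.5 (10% v 20%): 1.96 × √(0.255/60) = 0.128; √(0.25/60) = 0.0645; (0.100 − 0.128)/0.0645 = −0.43; power 33%.
- s = 0.25 (5% v 10%): power 18%.

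With 45 per arm and full capture, 20% v 40% has 54% power. Even complete data would give a wide interval, so an estimate with a confidence interval is more useful than a test.

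**Step 4. What the feasibility study can exclude.** It had n = 23 (Section 2). Section 7.2 reports no harm but gives no event count. If there were 0 events in 23, the one-sided 95% upper bound on risk is 1 − 0.05^(1/23) = 12.2%. A true risk of 5% would give no events in 0.95^23 = 31% of such studies. Both figures rest on the assumed zero, and on all 23 having had the training and been asked.

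**The case against.** The strongest reply is that aggression is measured. Aggression regulation is a declared target, the ZECV is given to everyone, and Section 8.2 tests the risk factors two-sided, so worsening in the training arm could show. The MANSA item adds own offending. This stands against any inference that the trial does not measure aggression at all. It does not close the gap: the ZECV rates how anger is expressed and controlled and stops at follow-up I, and an accusation is a coarse stand-in for an act.

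Other stronger readings also fail:

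- **Aggression is the only harm named.** It is not. Sections 7.2 and 8.6 name muscle pain and bruises, and 8.6 also names scanner noise and confronting questionnaires.
- **The reassurance rests only on 23 people.** Section 7.2 also cites earlier work on exercise and psychomotor therapy, and Section 1 cites martial-arts studies.
- **Detection differs by arm.** The Summary gives controls 20 befriending sessions, and the available text does not say how these are observed. A difference is possible but not shown. Closer watching of the training arm would add events there, which does not favour the training.
- **The whole CTS2 will be scored as victimization.** No section says so, and the stated purpose points to the target items. Scoring may be settled in an analysis plan that is not at hand.

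An analysis plan could also designate the own-attack items as harm. It could not supply answers to an adverse-event question that was never asked.

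Finally, having blinded interviewers ask about injuries in a kickboxing trial could reveal the allocation and weaken the blinding in Section 6.2. That objection is sound and shapes the fix.

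**Conclusion.** The point holds as a low-cost improvement; it does not invalidate the trial. The protocol fixes a passive rule for harms, discusses aggression as a safety matter, and gives no safety role to the one scheduled instrument that asks how often participants attacked someone. As written, it plans no between-arm comparison of own aggression.

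The loss cannot be computed from the documents. In the illustration, catching between 75% and 25% of cases cuts power from 67% to between 50% and 18%. This depends on the assumed 20% and 40%, on equal capture in the arms and on full CTS2 capture. CTS2 answers are self-reports by unblinded participants, so they too will be incomplete and open to reporting bias. They are nevertheless asked of everyone at fixed times, unlike volunteered events. The 12% bound holds only if 0 of 23 had events, and the finding does not depend on it.

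**What to change.** 1. **Sections 6.1.2 and 8.2, victimization score.** State that the CTS2 victimization score uses only the attack items in which the participant is the target, leaving out the own-behaviour and negotiation items.
2. **Section 8.2, safety outcome.** Pre-state the own-attack items of the CTS2 as a safety outcome, compared between arms at post-test and at each follow-up, with an estimate and confidence interval.
3. **Section 7.2, collection.** Add a brief standard adverse-event question in both arms at the existing assessments. Make it self-completed and keep the answers from the blinded interviewers, so that they do not learn the allocation.

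The first two changes need no new data. The cost is one more analysis, one short item per visit and more minor events on record. No treatment or eligibility rule changes.
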